## Abstract

**Background:**

There is evidence to support the use of supplementation with long-chain omega-3 polyunsaturated fatty acids (LCn-3PUFA) from oily fish or fish oil for the treatment of various inflammatory diseases such as rheumatoid arthritis. Chronic obstructive pulmonary disease (COPD) is a progressive, terminal disease characterized by persistent airflow limitation, lung and systemic inflammation. To date, one randomized controlled trial has been published that assessed the efficacy of LCn-3PUFA in people with this condition. The aim of this article is to discuss the feasibility of conducting a trial to evaluate fish oil supplementation as adjunct therapy in people with COPD.

**Methods/Design:**

A 16-week parallel, double-blind, randomized, placebo-controlled dietary supplementation trial will be evaluated. Forty participants meeting spirometric and clinical criteria for COPD will be recruited from metropolitan Adelaide, South Australia. Participants will be randomized by minimization, based on a score derived from the modified Medical Research Council Scale for breathlessness, to receive 6 g/day of fish oil (approximately 3.6 g/day of LCn-3PUFA), or placebo (6 g/day of corn oil) capsules. Feasibility outcomes (recruitment, retention, supplement adherence, and time lost to exacerbation) and scientific outcomes (effect size and estimates of variance for inflammatory biomarkers, incorporation of LCn-3PUFA into erythrocytes, small airways function, dyspnea and functional exercise capacity) will be assessed pre- and post-intervention. Key feasibility criteria include recruitment of 40 participants in 52 weeks, 75% participant retention rate, 2% increase in the proportion of long-chain omega-3 fatty acids in erythrocytes, and a positive moderate effect size in at least three efficacy measures.

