### Feasibility outcomes and criteria

Within the four domains of feasibility (process, resources, management and scientific) there are specified outcomes in the process and resource domains that will be assessed throughout the study against feasibility criteria (see Table 2).

**Table 2 T2:** Feasibility outcomes and key feasibility criteria

**Outcome**	**Outcome measure**	**Key feasibility criteria**
*Process*		
Recruitment rate	Number of participants recruited per week.	Recruit 40 participants in 52 weeks.
Retention rate	Number of participants completing the intervention.	Complete the intervention in 80% of all recruited participants.
Supplement adherence rate	Symptom diary.	
	Change in RBC total LCn-3PUFA content.	≥2% change in total RBC LCn-3PUFA.
	Capsule count at study completion.	≥80% of capsules consumed.
Refusal rate	Number of identified volunteers who decline to participate/randomize.	
Time lost to exacerbation	Symptom diary.	
*Scientific*		
Supplement safety	Reported symptoms from supplement.	
Estimate effect size	Listed scientific outcomes.	A positive moderate effect size (≥0.2) in at least CRP, dyspnea and FEF_25-75_.
Estimate variance	Standard deviations of listed outcomes.	

CRP, C-reactive protein; FEF_25-75_, forced expiratory flow between 25 and 75% of forced vital capacity; LCn-3PUFA, long chain omega-3 polyunsaturated fatty acid; RBC, red blood cell.

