#### Process outcome measures

A number of process outcomes will be assessed throughout the study including participant recruitment and retention, supplement adherence, time lost to exacerbation and participant experiences and perspectives about participating in the study. Participant recruitment and retention will be assessed descriptively by recruitment and refusal rates, while retention will be determined by the number of enrolled participants who complete the study protocol.

Supplement adherence will be assessed in three ways. Firstly, by determining changes from baseline to post-intervention in the LCn-3PUFA content of erythrocytes, as the LCn-3PUFAs are incorporated into erythrocyte membranes in a dose-dependent and time-dependent manner [41]. Secondly, a symptom diary will be used to document self-reported supplementation consumption including whether the capsules were consumed each day, how many capsules were consumed and whether any side effects were experienced such as eructation or heartburn. Thirdly, participants will be asked to return all unused capsules at the completion of the study and the remaining capsules will be counted.

The time lost to exacerbation (change in usual symptoms potentially leading to a change in medication, change in usual activities or unscheduled visit to a doctor) will be determined using a symptom diary in the format of one month per page. The diary enables the assessment of exacerbation frequency and severity during the supplementation period. The number of exacerbation days will be counted from the diary, while an exacerbation severity score will be calculated using methods adapted from those described by Effing *et al*. [42]. Data collected from the symptom diary will be used to determine the frequency of exacerbation, whether periods of exacerbation impact upon supplement consumption and whether periods of exacerbation have a confounding effect on supplementation or study outcomes. This information will be used to determine whether exacerbations during the supplementation period should be an exclusion criterion in a subsequent study.

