#### Blood biomarkers

Venous blood samples will be obtained after a 10 to 12-hour overnight fast by venepuncture (EDTA-containing tubes) and will be centrifuged within two hours of sampling. Plasma will be removed and erythrocytes will be washed with saline. Aliquots of plasma and erythrocytes will be stored at −80°C until analysis. Relative proportions of individual fatty acids in erythrocyte phospholipids will be assessed using a method adapted from previously established methods [43-45] and described in detail by Milte *et al*. [46]. In this process fatty acids will be extracted and transmethylated and the methyl esters will be separated and quantified using a Shimadzu 2010 gas chromatograph (Shimadzu, Milan, Italy). Fatty acid methyl esters will be identified by comparing retention times to those of authentic lipid standards (GLC-463, Nu-Chek Prep Inc. Elysian, MN, USA). Inflammatory biomarkers including tumor necrosis factor (TNF-α), interleukin-1 beta (IL-1β) and interleukin-6 (IL-6) and the anti-inflammatory biomarker interleukin-10 (IL-10) will be analyzed in duplicate using multiplex Luminex analyzer (Luminex B.V., Oosterhout, The Netherlands) assays. Intra- and inter-assay coefficients of variation (CV) are 5 to 14% and 4 to 18%, respectively. High sensitivity C-reactive protein will be measured using an automated spectrophotometric analyzer (Konelab, Model 20xTi; Thermo Electron, Waltham, MA, USA); the CV for this determination is 2.3%.

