### Data analysis

SPSS version 17 for WINDOWS [International Business Machines Corporation (IBM), New York, USA] will be used for analyses. Data will be cleaned, checking for errors or missing values. Continuous data will be checked for normality of distribution and non-normally distributed data will be transformed where possible. Scatter plots will be used to determine nature/shape of relationships before applying linear regression.

The primary focus of this study is feasibility, which will be analyzed using descriptive statistics and frequency tables. The key feasibility outcomes are:

1. Recruit 40 participants in 52 weeks;

2. Complete the intervention in 75% of all recruited participants;

3. ≥2% change in total erythrocyte LCn-3PUFA and ≥80% of capsules consumed (estimated from remaining capsules);

4. A positive moderate effect size (≥0.2) in at least three scientific outcome measures (between active and placebo groups).

Analysis of variance (ANOVA) with repeated measures will be used to estimate the effect size of LCn-3PUFA versus placebo supplementation on the scientific outcome measures (six-minute walk, pulmonary function tests, questionnaire scores, blood biomarkers of inflammation and symptoms (for example, high sensitivity C-reactive protein, dyspnea and impulse oscillometry)). Progressive Bonferroni corrections will be used to correct for the effects of multiple outcomes. Comorbid status and severity of exacerbations will be assessed as potential confounders using multiple regression analysis.

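### The effect-size go-criterion does not say whether erythrocyte LCn-3PUFA, already the adherence measure, may count as one of the three qualifying outcomes, and the protocol's own sections point both ways

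*Protocol article*

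**What the plan says.** **As a scientific outcome.** The Methods/Design paragraph of the Abstract lists "scientific outcomes (effect size and estimates of variance for inflammatory biomarkers, incorporation of LCn-3PUFA into erythrocytes, small airways function, dyspnea and functional exercise capacity". The assay itself is described in Blood biomarkers, a subsection of Scientific outcome measures: "Relative proportions of individual fatty acids in erythrocyte phospholipids will be assessed".

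**As adherence.** Process outcome measures makes it the first of three adherence checks, "by determining changes from baseline to post-intervention in the LCn-3PUFA content of erythrocytes", on the ground that "LCn-3PUFAs are incorporated into erythrocyte membranes in a dose-dependent and time-dependent manner". Table 2 places "Change in RBC total LCn-3PUFA content" under Process, in the supplement adherence row, with the criterion "≥2% change in total RBC LCn-3PUFA". Data analysis item 3 repeats that threshold alongside 80% capsule consumption.

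**The effect-size criterion** is worded in three ways:
- Data analysis, item 4: "A positive moderate effect size (≥0.2) in at least three scientific outcome measures (between active and placebo groups". No outcome is named.
- Abstract: a positive moderate effect in three or more efficacy measures. None is named, and the erythrocyte increase is listed beside it as a separate criterion.
- Table 2: at least 0.2 in CRP, dyspnea and FEF25-75.

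The sentence after item 4 lists what the repeated-measures ANOVA will cover: walk test, lung function, questionnaires, inflammatory blood markers and symptoms. Erythrocyte fatty acids are not in it.

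**The concern.** Erythrocyte LCn-3PUFA is a marker of intake. Fish oil and corn oil groups should differ on it whenever capsules are swallowed, whether or not fish oil does anything for COPD. If it may count among the three scientific outcomes of item 4, good adherence already delivers one of the three effects, and only two real signals are still needed. The same measurement would then help to satisfy both item 3 and item 4.

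These criteria feed the decision on a larger trial. Which outcomes qualify should not depend on which section an analyst follows once the results are known. This is not a detail left to a fuller document: the article states the criteria and classifies the outcomes itself, and does so inconsistently.

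**Working it through.** **Inputs from the protocol.** Sample Size gives 40 enrolled, 25% dropout and 30 completers. The figure reproduces: 30 / (1 − 0.25) = 40. The threshold is 0.2 (Data analysis item 4 and Table 2).

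**Assumptions, since the protocol does not give these.** Equal arms, so 15 completers each; effect size read as a standardised mean difference *d*, signed so that positive is beneficial; no true effect on any outcome other than uptake; *k* other qualifying outcomes, with a common correlation of 0 or 0.5.

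**Step 1: one null outcome.** SE(*d*) = √(2/15) = 0.365. P(*d* ≥ 0.2) = 1 − Φ(0.2/0.365) = 1 − Φ(0.548) = 0.292.

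**Step 2: uptake itself.** Read the 2% criterion as percentage points and suppose that it is the between-group difference. No SD is given, so take 1, 2, 3 or 4 points. Then *d* = 2.0, 1.0, 0.67 or 0.5, and by the noncentral *t* with 15 per arm P(observed *d* ≥ 0.2) = 1.00, 0.99, 0.90 or 0.80. Uptake is close to a free pass unless its SD is large.

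**Step 3: chance of meeting item 4.** If uptake is excluded, three of the *k* others must pass; if it counts and is taken as certain, two must pass. For *k* = 4, independent:
- P(≥3) = 4(0.292³)(0.708) + 0.292⁴ = 0.078
- P(≥2) = 1 − 0.708⁴ − 4(0.292)(0.708³) = 0.334

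Other cells are from the binomial or from simulation with 400,000 draws.

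| Other outcomes *k* | Independent: excluded → counted | Correlation 0.5: excluded → counted |
|---|---|---|
| 4 | 0.08 → 0.33 | 0.18 → 0.34 |
| 8 | 0.43 → 0.73 | 0.39 → 0.53 |
| 12 | 0.73 → 0.91 | 0.51 → 0.62 |
| 20 | 0.96 → 0.99 | 0.63 → 0.72 |

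Treating uptake as certain gives an upper bound. If it passes with probability 0.80, independently of the rest, the *k* = 8 figure is 0.80 × 0.73 + 0.20 × 0.43 = 0.67 instead of 0.73.

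**Step 4: Table 2's rule.** All three named outcomes must pass: 0.292³ = 0.025 if independent, 0.10 at correlation 0.5. Uptake is not among them, so its contribution is zero.

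**Step 5: which *k* is realistic.** The Scientific outcome measures section names five blood markers other than fatty acids, FEV1, FVC, IC, VC, four FEF measures, oscillometry, gas transfer, lung volumes, Dyspnoea-12, two visual analogue scales, mMRC and walk distance. That is 5 + 4 + 4 + 1 + 1 + 1 + 1 + 2 + 1 + 1 = 21 before HADS and the CRQ domains. If item 4 is read literally, the lower rows of the table are the relevant ones.

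**The case against.** A reader might infer that the protocol definitely counts uptake twice. It does not say so. Nowhere is erythrocyte LCn-3PUFA named as one of the three effects. Table 2 names three others, the ANOVA list leaves it out, and the Abstract keeps the erythrocyte increase apart from its efficacy measures. The assay may sit under Blood biomarkers only because it uses the same blood sample. All of this stands, and it limits the point to a conflict between sections.

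It does not settle the conflict. Table 2 cannot be presumed to govern: it asks for 80% retention where Data analysis and the Abstract ask for 75%, and on the effect-size rule too those two agree with each other in naming no outcomes. Table 2's own measure for the effect-size row is the listed scientific outcomes, and the Abstract's list includes uptake. The ANOVA list disagrees with the Abstract, which promises an effect size for incorporation. The term efficacy measures is not defined.

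Two further inferences go too far. The fourfold rise from 0.08 to 0.33 belongs to four other outcomes only; with about 20, item 4 is easily met by chance even without uptake, and counting it adds roughly 3 to 10 percentage points. Nor would items 3 and 4 cease to be separate tests: item 3 still needs the capsule count, and item 4 still needs two other outcomes.

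It is also fair to say that estimating the effect on incorporation is a legitimate scientific aim, being an early step in the proposed mechanism. That stands, and the remedy should respect it.

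**Conclusion.** The point holds as an unresolved conflict in a decision rule. Erythrocyte LCn-3PUFA is classed both as a scientific outcome with an effect size and as the adherence measure with its own criterion, and item 4 does not exclude it. Under item 4's wording, intake alone could very probably supply one of three required effects; under Table 2 it could supply none. The documents do not support the claim that it will be counted.

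The consequence ranges from nil (Table 2) to a gain of about 30 percentage points (eight other independent outcomes). With the long outcome list that the protocol actually describes, it is about 3 to 10 points. These figures rest on 15 completers per arm, a standardised mean difference, no true effect elsewhere, certain uptake, and assumed values for the number of outcomes and their correlation. Within item 4's wording the direction is the same throughout: counting uptake makes the criterion easier to meet without evidence of benefit.

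**What to change.** 1. Use one list of qualifying outcomes for the effect-size criterion, identical in the Abstract, Table 2 and Data analysis item 4, so that the named-trio and any-three versions are reconciled.
2. Add to item 4: *Erythrocyte fatty acids are judged under item 3 only and do not count toward the three outcomes.*
3. Leave incorporation in the study's reporting. Its effect size and variance may still be estimated and presented as a measure of uptake, so it need not be removed from the scientific outcomes.

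The cost is a sentence in Data analysis and aligned wording in two other places, with no new data or procedures. The status given is not yet recruiting, so this can be settled before any results exist. The downside is a slightly harder criterion than item 4's present wording allows.

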**Discussion:**

There are a number of challenges in designing supplementation intervention studies with this population. These include the lack of prior data from which to select appropriate primary outcomes or to estimate effect sizes, and the feasibility of continuous supplementation in a population characterized by multiple comorbidities and a high likelihood of exacerbations, potentially requiring hospitalization or change in medication. Upon completion of this protocol, feasibility outcomes will guide the direction of future multicentre dietary interventions in this population.

**Trial registration:**

Australia and New Zealand Clinical Trials Register (ANZCTR): ACTRN12612000158864

## Background

Chronic obstructive pulmonary disease (COPD) is a progressive lung disease characterized by irreversible airway obstruction and systemic inflammation [1]. In 2008, COPD was the fourth leading cause of death worldwide [2], and is predicted to be the third leading cause of death by 2030 [3]. Airway obstruction is caused by inflammation of the bronchi leading to increased mucus secretion (chronic bronchitis) and destruction of lung parenchyma leading to distal airway dynamic compression (emphysema). Air flow is further limited by structural changes that occur as a result of chronic inflammation [1]. The clinical signs and symptoms of COPD include dyspnea, productive cough, wheeze, fatigue, reduced exercise tolerance and repeated respiratory infections. Exacerbations (acute worsening of symptoms leading to a change in medication or management) caused by infection, change of season and air pollution, commonly occur in people with COPD and contribute to the overall severity of the disease [1]. The perception of breathing discomfort known as dyspnea, is one of the most common life impairing symptoms of COPD [4]. Dyspnea restricts and reduces physical activity in people with COPD, which over time leads to a more sedentary lifestyle, reduces cardiorespiratory fitness and quality of life [4].

In people with COPD, both airway and systemic inflammation occur. It is unclear whether systemic inflammation is pathological or results from an overflow of inflammatory mediators from the lung [5]. Nonetheless, the systemic inflammation associated with COPD can impair skeletal muscle function and mass, cardiovascular function, skeletal integrity and mental health, and therefore increase the risk of diseases such as osteoporosis, cardiovascular disease, diabetes and depression [5-8]. Dietary interventions which have been shown to be beneficial in the treatment of inflammatory diseases such as rheumatoid arthritis and cardiovascular disease, such as supplementation with long-chain omega-3 polyunsaturated fatty acids (LCn-3PUFA), might also be beneficial for people with COPD.

Polyunsaturated fatty acids (omega-3 and omega-6) are essential fatty acids that must be consumed in the diet as the human body is unable to synthesize them. They can be further desaturated and chain elongated to form LCn-3PUFA or LCn-6PUFA, respectively. The major LCn-3PUFAs, docosahexaenoic acid (DHA) and eicosapentaenoic acid (EPA), can also be sourced directly from consumption of fish, while the major long-chain omega-6 fatty acid (LCn-6PUFA), arachidonic acid (AA), can also be sourced through the consumption of meat, dairy and eggs [9]. Both LCn-3PUFA and LCn-6PUFA are essential for functions in multiple systems in the body, but are particularly important in the inflammatory response. The metabolism of omega-3 and omega-6 fatty acids have different effects in the body: EPA produces less potent inflammatory eicosanoids than AA; EPA, DHA and AA differ in their roles as mediators of inflammation resolution [10]. Increased consumption of EPA and DHA results in proportional increases of these fatty acids in inflammatory cells at the expense of AA [11].

The production of inflammatory mediators is also influenced by LCn-3PUFA at a cellular level through changes in gene transcription. An important gene transcription factor in the inflammatory response is nuclear factor kappa beta (NF-κB), which must be activated before it can translocate into the nucleus to commence gene transcription [10,12]. It is suggested that DHA and EPA are able to inhibit the activation of NF-κB, thereby reducing the transcription of a number of inflammatory cytokines and chemokines [10].

A preliminary review of the literature was conducted in March 2013. Major databases with a health focus (for example, Medline, Embase, Cochrane Library) and English language clinical trial registries (for example, Clinical Trials.gov) were searched for studies that investigated the intake of polyunsaturated fatty acids (PUFAs) in human adults with COPD. Conference abstracts were excluded. This search identified five published studies and three study protocols (one of which is the proposed study); details of these studies can be found in Table 1. An additional published study was identified although the study has been retracted due to falsified data and was therefore excluded [13].

**Table 1 T1:** Summary of published studies and proposed trials of omega-3 fatty acid supplementation in chronic obstructive pulmonary disease (COPD)

Duel-Energy X-ray absorptiometry	No	No	No	No	No	No	Yes	No
Statistical test	Linear regression	Logistic regression	Nonlinear regression	Logistic regression	Logistic regression	Association between n-3 intake and endothelial function	Association between n-3 intake and protein synthesis	ANOVA
	Comparison PUFA and placebo group after 8 week intervention.	Association between n-3 intake and COPD	Association between n-6 intake and COPD	Association between PUFA and biomarkers	Association between PUFA intake and COPD			
Results	Greater ↑ exercise capacity in PUFA compared to placebo group*.	COPD strongly and inversely associated with intake of n-3 fatty acids*^b^	No association between COPD and n-3 intake.	↑ ALA associated with↓ TNF-α *^a^	↑ prevalence COPD associated with, ↓ PUFA intake *^b^, ↓ n-6 intake *^b^, ↓ n-3 intake *^b^	N/A	N/A	N/A
			↑ intake of four of the n-6 fatty acids associated with ↑ risk of COPD*^c^.	↑ LA and AA associated with ↑ CRP *^c^				
	PUFA no effect on FEV_1_ or muscle strength.							
	No change in blood biomarkers in either group.			↑ AA associated with ↑ IL-6 *^c^				

A, active; ALA, alpha linoleic acid; ANOVA, analysis of variance; AA, arachidonic acid; CRP, C-reactive protein; DHA, Docosahexaeneoic acid; EPA, eicosapentaenoic acid; FEV1, forced expiratory volume in 1 second; FFQ, food frequency questionnaire; GOLD, Global initiative for chronic obstructive lung disease; HADS, Hospital anxiety and depression scale; IL-6, interleukin-6; LA, linoleic acid; n-3, omega-3 fatty acid; P, placebo; PBD, Post bronchodilator; PUFA, Polyunsaturated fatty acid; QOL, quality of life; 6MWD, six-minute walk distance; TNF-α, tumor necrosis factor-alpha.

*Statistically significant *P* <0.05 ^a^ odds ratio <1, ^b^odds ratio ≥1.0, ^c^odds ratio ≥1.5.

PUFA refers to both omega-3 and omega-6 fatty acid intake.

^d^ PUFA blend consists of 400 mg stearidonic acid, 760 mg gamma-linolenic acid, 1,200 mg alpha-linolenic acid, 700 mg eicosapentaenoic acid and 340 mg docosahexaenoic acid.

^e^Weighted mean.

Broekhuizen *et al*. [14] investigated the effects of PUFAs on the outcome of pulmonary rehabilitation (exercise capacity and reversal of muscle wasting). This study compared the effects of eight weeks of pulmonary rehabilitation combined with a total daily PUFA dose of 3.4 g/day (400 mg stearidonic acid, 760 mg gamma-linolenic acid, 1,200 mg alpha-linolenic acid (ALA), 700 mg EPA and 340 mg DHA) versus a placebo (palm and sunflower oils) in 102 people with COPD. All other included published studies [15-18] investigated associations between omega-3 intake and COPD prevalence or inflammation in different populations.

Overall the results of the five studies varied. Broekhuizen *et al*. [14] reported an increase in maximum load (incremental maximal test) and an increase in duration (fixed load submaximal) bicycle ergometry tests for both groups; however the increase in the PUFA group was significantly greater than the placebo group. PUFA supplementation had no effect on muscle strength or FEV_1_ and neither PUFA supplementation nor pulmonary rehabilitation affected biomarkers of inflammation [14]. McKeever *et al*. [17] reported no significant association between LCn-3PUFA and COPD. Both Shahar *et al*. [18] and Hirayama *et al*. [16] reported inverse associations between LCn-3PUFA intake and the prevalence of COPD, while de Batlle *et al*. [15] reported negative associations between LCn-3PUFA intake and concentrations of inflammatory markers. In studies that reported an association between intake of omega-3 or omega-6 fatty acids and COPD, the strength of the associations was predominantly small (odds ratio 1.5 to 3.5 [19]).

Excluding the current protocol, the search of the clinical trials registries identified two randomized controlled trials currently underway (University of Columbia [20] and Texas A&M University [21]). The University of Columbia study is a pilot randomized controlled trial with a lower dose of LCn-3PUFA (2.5 g/day DHA + EPA) than the proposed study, but for a longer supplementation period. The Texas A&M University randomized controlled trial has a similar dose to the proposed study (3.5 g/day DHA + EPA) but for a shorter supplementation period (8 weeks). There are similarities between the three studies (for example, outcomes and omega-3 dose) although the primary focus of the three proposed studies differs, with Columbia University focusing on endothelial function, Texas A&M focusing on muscle repair and damage, while the proposed study focuses on feasibility for a larger RCT.

In theory, LCn-3PUFA from fish oil may improve efficacy of current treatments for COPD by reducing inflammation. Given the paucity of data for fish oil supplementation trials in people with COPD, there are currently no data to guide study design decisions such as appropriate outcome measures (including the primary outcome), likely effect sizes or sample size determination. COPD is a complex condition where comorbidities and exacerbations are to be expected, both of which may confound the effect of, or adherence to supplementation. In addition, slow recruitment and high dropout rates have been reported in intervention trials for people with COPD [22-24]. The driver for this proposed research is the hypothesis that LCn-3PUFA supplementation as an adjunct therapy will improve health outcomes in people with COPD. However before this hypothesis can be tested, it is important to establish the feasibility of the study protocol and justification for continuing to a larger study.

While the terms ‘pilot study’ and ‘feasibility study’ are often used interchangeably in the literature, Arain *et al*. [25] explains the distinction between the two. A feasibility study seeks to determine if the study is possible, with the available resources and in the current circumstances. A pilot study is used to determine the efficiency of the study protocol as a whole. Thabane *et al*. [26] and van Teijlingen *et al*. [27] recommend undertaking a feasibility study in order to determine recruitment rates, estimate variability of outcomes to assist with sample size calculations or to obtain data to support a funding application.

Given the lack of pre-existing data on which to inform primary outcome and sample size estimates and the known complexities of undertaking intervention studies in people with COPD, this study aims to determine the feasibility of undertaking a randomized controlled study of daily LCn-3PUFA supplementation in people with COPD. The objectives of this study are to determine feasibility within two domains including process (for example, recruitment and retention rates) and scientific (for example, estimate of effect size and variance in outcomes).

